# Cognitive behavioural therapy in comparison to treatment as usual in young adults at high risk of developing bipolar disorder (Bipolar At Risk): a randomised controlled trial to investigate the efficacy of a treatment approach targeted at key appraisal change: Bipolar At Risk Trial II (BART II)

**DOI:** 10.1186/s12888-025-06973-3

**Published:** 2025-07-01

**Keywords:** Bipolar at risk, Bipolar disorder, Mood swings, Early intervention, Early detection, Cognitive behavioural therapy, Randomised controlled trial, Prevention, Psychological therapy, Youth mental health

## Abstract

**Background:**

Research has demonstrated the ability to identify and treat individuals at high risk of developing psychosis. It is possible to use a similar strategy to identify people who have an emergent risk of bipolar disorder (BD). Interventions during the early phase may improve outcomes and reduce risk of transition. Criteria have been established to identify individuals considered to be at high risk for developing BD, also known as Bipolar At Risk (BAR). Offering a psychological intervention may provide the possibility of prevention. Evaluating efficacy and the mechanisms by which this treatment works is now required.

**Methods:**

A multicentre, rater-masked randomised controlled trial with two parallel arms will compare cognitive behaviour therapy (CBT) for young people meeting BAR criteria (CBT_BAR_) + Treatment as Usual (TAU) vs. TAU alone. Participants will be recruited from five National Health Service (NHS) sites in the UK. Outcome and mediational variables will be collected at baseline, 17-weeks (in treatment), 27-weeks (post-CBT_BAR_ /TAU), and 52-weeks. Qualitative work will examine the perceived mechanisms of change and implementation of CBT_BAR_ in the NHS.

**Discussion:**

Our efficacy hypotheses are CBT_BAR_ + TAU (compared to TAU alone) will lead to improvement in mood swings, a reduction in the likelihood of transition to BD, and improvements to functioning and quality of life. Our mechanistic hypothesis is CBT_BAR_ + TAU causes improvement in mood swings due to the reduction of extreme positive and negative appraisals of internal states which in turn improves subsequent behaviours used to control mood and then internal states. Our trial will explore the perceived mechanism of change via this novel intervention (CBT_BAR_) and if the approach can be implemented within current services in the UK.

**Trial registration/Status:**

The trial protocol is registered with ISRCTN (ISRCTN13363197, registered on 25th January 2023). Recruitment started in February 2023 and is ongoing.

**Supplementary Information:**

The online version contains supplementary material available at 10.1186/s12888-025-06973-3.

## Background

An estimated 1–3% of the population are affected by Bipolar Disorder (BD) [1, 2], which poses particular risks for young people. At least 25–50% of people with BD attempt suicide at least once [3], with the World Health Organisation identifying BD as a major cause of mortality and morbidity in youth (aged 10–24) [4]. With an average duration of untreated illness (DUI) of 6–10 years [5], those with adolescent onset have prolonged DUI [6] leading to increased mood episodes and elevated suicide risk [7]. This is particularly significant given that BD has the highest suicide rates among psychiatric diagnoses [8], with deaths often occurring in those with longer illness duration [9]; therefore, there is a unique opportunity for early intervention to change this trajectory.

The James Lind Alliance identified priorities for those with BD including rapid access to diagnostic assessments, developing effective talking therapies such as cognitive behaviour therapy (CBT) and individually tailored treatments [10]. Early interventions in psychosis services show health and economic benefits [11] and youth service models propose to widen intake criteria to encompass BD and those at risk of BD with the aim of reducing symptoms and risk of progression to more severe illness [12]. Extending early intervention and early detection services to include BD could yield £35 m savings in the UK [13], particularly for those meeting bipolar at-risk criteria (BAR) [14, 15], and who are help seeking, distressed National Health Service (NHS) patients.

Early detection of BD has focused on familial risk [16–19] and identification of state-trait factors [12]. Detection of those at risk for BD is possible using standardised criteria. BAR criteria [14, 15] consist of youth (16–25) experiencing distressing high mood; and/or high and low mood swings; and/or a first degree relative with BD plus depressed mood. This has predictive validity, can be reliably assessed (in an NHS context), holds clinical utility and is suitable for numbers needed to screen [5]. Most people meeting BAR criteria present with depressed mood (often atypical depression) [20] and mood swings which are generally poorly recognised and misdiagnosed. This leads to inappropriate treatments e.g. antidepressants which can induce mania [21], or psychological treatments for unipolar depression that do not target modifiable risk factors for atypical depression or mood swings. BAR individuals are 100 times more likely to convert to first-episode mania than the general population, and 20 times more likely than those with unipolar depression [22, 23], representing a unique chance to intervene.

Minimal evidence exists about effective treatment options for those meeting BAR criteria. National Institute for Health and Care Excellence (NICE) guidelines recommend offering people with BD psychological interventions (CBT) [24]. For children and young people, pharmacological treatment is only recommended when symptoms are severe [24]. Treatment access is difficult and lengthy and duration of untreated illness is linked with poor outcomes [25]. Yet, it is possible to deliver treatments in routine services which can have beneficial effects [26]. Meta-analyses report the efficacy of CBT to reduce relapse and improve symptoms of depression, mania, and functioning in BD [27–31] and that it is cost-effective when compared with TAU [32]. A recent randomised controlled trial (RCT) found CBT significantly improved outcomes in recent onset BD [33], and studies of psychological therapies for young people with BD report benefits of CBT [34]. NICE do not yet recommend CBT as a treatment for BAR individuals due to no consensus regarding early screening and lack of quality trials [24]. A rigorous RCT is needed to evaluate the efficacy of CBT to reduce distressing mood swings and understand to what extent CBT reduces mechanisms central to a model of mood swings [35]. A review assessing pharmacological interventions for BAR found a lack of high-quality research on preventative treatments [36], so could not conclude whether pharmacological approaches are beneficial or harmful. Coupled with potential safety considerations, psychological interventions might have an advantage over pharmacological interventions [37], particularly since pharmacological treatments are not always successful for established BD.

To address this evidence gap, we conducted a feasibility trial (Bipolar At Risk Trial (BART), conducted from 2015 to 2018), funded by the National Institute for Health Research (NIHR) Research for Patient Benefit (RfPB) programme (PB‐PG‐1013‐32,044). The results highlighted the 76 participants meeting BAR criteria were help-seeking, distressed NHS patients, with complex and co-morbid difficulties, and in need of specialist intervention [38]. These findings are similar to those reported by Bechdolf [15] who evidenced high levels of unemployment, suicide attempts and Axis I disorders. Participants’ treatment pathways demonstrated the breadth of treatments and services that people had accessed for help. The BART feasibility trial showed the CBT intervention was safe and acceptable, and signalled positive therapeutic effects. It was a single-site study completed in Greater Manchester; considered a large and diverse city but may not be fully representative of the wider BAR population. A larger, multi-site RCT is needed to expand the evidence base of effective treatments for NHS patients and understand any potential mechanisms by which this treatment may improve clinical outcomes.

### Aims/Objectives

The overall aim is to conduct a two-arm multicentre, rater-masked, randomised controlled trial comparing CBT_BAR_ plus TAU vs. TAU alone for BAR individuals to evaluate the efficacy of a specific intervention (CBT_BAR_). We also aim to investigate how CBT_BAR_ impacts on the pathway between key psychological processes and mood swings (See Table 1. Aims, Objectives and Outcomes). The overarching research questions are:

**Table 1 Tab1:**
[figure not shown]
Aims, objectives and outcomes

To what extent is CBT_BAR_ (a psychological therapy) effective in reducing distressing mood swings compared with TAU for BAR individuals? (at 27-weeks)To investigate the extent to which CBT_BAR_ impacts on the pathway between key psychological processes and mood swings (at 17-weeks).What are the perceptions of patients and heath care professionals regarding the implementation of therapy in NHS services?

## Methods

### Trial design and flow chart

The BART II trial is a rater-masked, randomised controlled trial (RCT) with two parallel arms comparing a psychological intervention (CBT_BAR_) plus Treatment As Usual (TAU) to TAU alone (control condition). There will be two nested components: 1) a qualitative sub-study to understand the perceived mechanisms of change for participants offered the CBT_BAR_, as well as the implementation of CBT_BAR_ in NHS services; and 2) Inclusivity Workstream. Outcome and mediational variables will be collected at baseline, 17-weeks (during treatment window), 27-weeks (after therapy cessation) and 52-weeks. See Fig. 1 for the CONSORT flow diagram.

**Fig. 1 Fig1:**
[figure not shown]
CONSORT 2010 flow diagram: BART II

The trial was prospectively registered on the ISRCTN registry (ISRCTN13363197) prior to recruitment commencing. The study was funded by the Efficacy and Mechanism Evaluation (EME) Programme, an MRC and NIHR partnership (NIHR132622). All work has been developed and will be reported in line with CONSORT Extension to Randomised Controlled Trials (http://www.equator-network.org/reporting-guidelines/consort/), SPIRIT guidelines (http://www.spirit-statement.org/), and the TIDieR checklist (http://www.bmj.com/content/348/bmj.g1687) (see Supplementary Data). An independent Trial Steering Committee (TSC), Data Monitoring and Ethics Committee (DMEC) and multiple lived-experience advisory groups have been set up to provide guidance and oversight to the trial.

### Study setting

The trial will be conducted in five community-based NHS foundation trusts (UK): Greater Manchester Mental Health NHS Foundation Trust (GMMH), Lancashire and South Cumbria NHS Foundation Trust (LSCFT), Sheffield Health and Social Care NHS Foundation Trust (SHSC), Birmingham Women’s and Children’s NHS Foundation Trust (BWC), and Norfolk and Suffolk NHS Foundation Trust (NSFT).

### Participants

The inclusion/exclusion criteria are:

#### Inclusion criteria

i.16–25 years old,ii.Help seeking,iii.Able to provide written, informed consent, andiv.Meets criteria for at least one BAR group within the last 12-months (See Table 2).

**Table 2 Tab2:** Bipolar At Risk (BAR) groups (Adapted from Bechdolf [14] with modified group classifications)

BAR group name	Criteria as assessed by the Structured Clinical Interview for DSM-5 Research Version (SCID-5-RV)	Duration of symptoms
1. Subthreshold mania	Abnormally and persistently elevated, expansive or irritable mood and at least two criteria from the symptom list (three if mood is irritable): Inflated self-esteem/grandiosity; Decreased need for sleep; More talkative than usual or pressure to keep talking; Flight of ideas or racing thoughts; Distractibility; Increased goal-directed activity or psychomotor agitation; excessive involvement in activities that have a high potential for painful consequences	At least two consecutive days but < 7
2. Depression + cyclothymic features	Depressed mood or loss of interest/pleasure for at least one week and at least two criteria from the symptom list: Significant weight loss; Insomnia or hypersomnia nearly every day; Psychomotor retardation or agitation; Fatigue or loss of energy; Feelings of worthlessness or excessive/inappropriate guilt; Diminished ability to think or concentrate; Recurrent thoughts of death or suicidal ideation *Plus* *S*ubthreshold mania symptoms as described in group 1 (but see “Duration of symptoms”)	Depression: at least one week Subthreshold mania symptoms: four hours within 24-h period, on at least four cumulative, lifetime days
3. Depression + genetic risk	Depression symptoms as described in group 2 *Plus* First-degree relative with BD	Depression: at least one week

^*^When a participant meets more than one BAR group at baseline, the BAR group for randomisation input will be decided using a hierarchical rule, with BAR Group 1 entered when met, BAR Group 2 entered when met on own or in combination with BAR Group 3, and BAR Group 3 only entered when met alone

#### Exclusion criteria

i.History of a treated/untreated manic episode or psychosis of 1-week duration or longer,ii.Treatment with a mood stabiliser for longer than 6 weeks or antipsychotic for 3 weeks (that evidence exclusion on point above or at the time of the assessment whereby at-risk status cannot be confirmed),iii.Organic brain disorder,iv.Inability to complete assessments due to language barriers,v.Inpatient/acute psychiatric care needed, or primary substance abuse/dependency.

To ensure the study results are readily translatable within the current NHS, recruitment will involve outreach to a variety of services including children and young people’s mental health services, early intervention and detection teams (EDIT/EIT), Community Mental Health Teams (CMHT), Improving Access to Psychological Therapies (IAPT), primary care psychology services, GPs, schools, university health services, other youth services and the voluntary sector. Teams will be provided with study materials and be asked to identify potentially eligible individuals to refer to the research team. Referrers will discuss the study and obtain consent-to-contact for researchers who will then provide the individual with information to enable them to provide informed consent. Potential participants will be screened for potential eligibility before informed consent is taken. After written informed consent is obtained, BAR status will be established using the SCID-5-RV [39] and eligibility confirmed with the chief investigator or their delegate. Participants will be informed that they can withdraw from the trial at any point, without giving a reason and without it affecting their care.

### Inclusivity workstream

Data demonstrates significant health inequalities for people from UK ethnic minority groups, particularly in mental health treatment access/offer [40] and trial recruitment [41]. This is especially true of access to treatments which are preventative and early in the care pathway [42] versus differential higher rates within acute and secure pathways e.g. inpatient care and forensic services [43]. As there are no meaningful differences between ethnic groups in terms of the likelihood of screening positive for bipolar disorder [44] it is paramount that specific efforts to reach out to UK ethnic minority participants are required.

The BART II inclusivity workstream aims to deepen understanding of the needs of diverse communities we are seeking to help by; identifying underserved groups, assessing research acceptability, understanding barriers, developing solutions, and creating necessary resources to ensure the BARTII research methods and outcomes remain meaningful for all eligible populations.

This workstream will gather referral data, evaluate a co-produced animation aimed at enhancing recruitment of ethnic minority youth (16–25) via a Study Within A Trial (SWAT 220; SWAT220 [name], [name], [name], [name], [name], [name], [name], [name], [name] (2022 JUN 16 2222).pdf), explore service access experiences, and develop inclusive recruitment recommendations. A Patient and Public Involvement group comprising UK ethnic minority individuals will provide essential insight and oversight.

### Randomisation and masking

Following informed consent and entry to the trial, participants will be randomly allocated to one of two trial arms. Randomisation will be independent and concealed, using permuted stratified blocks (by site (5-levels) and BAR group (3-levels)) via a web-based system at York Trials Unit (YTU). Stata v18.0 [45] was used to generate the allocation schedules. Researchers will enter participant’s details into the randomisation system and the outcome communicated to the chief investigator, trial management and administrators. Participants, their GP, and referrers will be informed about the allocation via letter.

Assessor’s will be masked to treatment condition. Masking will be maintained using various measures including separate offices for therapists and research assistants, reminders about masking, protocols for message taking, and data security using passwords and encryption. Letters to participants and clinicians will contain a standardised statement about the need to maintain the masking process. Unmasking will be recorded, and where possible an independent assessor with whom the masking has not been broken will complete follow-ups.

### Study arms

#### Intervention arm: the CBT_BAR_ intervention plus TAU

The CBT_BAR _intervention uses a model [46], which draws on a cognitive model of mood swings (Integrative Cognitive Model; ICM) [47]. Appraisals of internal states are central to the ICM, and often have multiple extreme, personalised and conflicting meanings (positive and negative). These extreme appraisals give rise to competing strategies to control internal states resulting in ascent and/or descent behaviours (dependent on the goal in mind), which cause shifts in mood states. CBT_BAR_ is also informed by a cognitive model tested for young people at risk of psychosis [48] where intrusions are often interpreted as threatening. As such, safety-seeking behaviours are employed serving to maintain difficulties. Interpretations are driven by life experiences and beliefs and knowledge about the self, the world and others. CBT_BAR_ formulations guide interventions aimed at reducing distressing mood swings by (1) changing appraisals, (2) reducing unhelpful coping strategies, and (3) providing increased awareness of mood states and associated behaviours. Targeting appraisals of mood states and unhelpful coping behaviours as key mechanisms, reduces escalating mood swings, lowering the likelihood of transition to bipolar disorder and improving recovery and quality of life.

The CBT_BAR_ intervention [49] components broadly fall under three categories: 1. Core principles and values (trusting relationship, validation and normalising experiences, and collaborative goal setting); 2. Cognitive change strategies targeting appraisals; 3. Behavioural strategies aimed at modifying responses. It is delivered via 26 sessions within a 6-month intervention window and treatment follows four stages: assessment and engagement, change strategy phase, longitudinal formulation phase and consolidation phase. Sessions are flexible, allowing for in person or online delivery by trial therapists (Clinical Psychologists and Psychological Therapists).

### Control arm: TAU only

The control condition is TAU plus follow-up. Referrers will be instructed to not withhold treatment. TAU may include standard psychiatric care, psychological and vocational interventions from various agencies (although, in our experience, provision for this population is poor). Access to services includes IAPT, Children and Adolescent Mental Health Services (CAMHS), Primary Care, Early Intervention Teams and CMHTs. CBT_BAR_differs from standard NHS treatment for young people with mood swings as highlighted in our feasibility trial [38]. All routine or additional treatments in both conditions will be monitored using a Treatment Documentation Sheet and specific treatments (anti-depressant and psychotherapy treatment) monitored within the LIFE [50] assessment tool.

TAU represents an enhancement over routine care since symptoms of mania will be detected earlier than in usual practice and appropriate treatment referrals made. Participation in assessments may reduce the (frequently high) number of contacts required to receive appropriate treatment for BD. Assessments may identify untreated BD and any risks to self or others that require immediate action. TAU alone will not include liaison with a clinical team, except where risk is concerned.

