### Assessments and outcomes

Assessors masked to treatment group will collect outcome variables at baseline, 17-weeks, 27-weeks (after therapy cessation/TAU), and 52-weeks (see Fig. 2 for schedule of enrolment, intervention and assessments). Assessments will be via semi-structured interviews and self-report questionnaires. Participants will be compensated for the time taken at each data collection point (£20). Contact will be made at 39-weeks to promote retention and re-confirm contact details. Participants will have flexibility to choose when and where they would like to be seen e.g. in non-stigmatising settings such as their home, youth centres, colleges, or primary care centres. Measures to be collected are listed below.

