#### Co-primary mood outcome measure

The SCID-5-RV with Psychiatric Status Ratings (PSR), which incorporates the SCID Longitudinal Follow-Up Evaluation (LIFE) [50], is used to assess the severity of depressive and manic symptoms over the prior 4 weeks, with measurements taken at the 27-week timepoint. Two scores are provided, depression (on which the sample size is primarily based), and mania.

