### Health economics measures

Measures collected to inform health economic analysis include:EQ-5D-5L [66] measure of health status is a generic measure for describing and valuing health on 5 domains: Mobility, Self-Care, Usual Activities, Pain/Discomfort, and Anxiety/Depression, and overall health.Recovering Quality of Life (ReQoL-10) [67] measures domains that are relevant to the recovery of people with mental health difficulties.Service use questionnaire adapted from previous trials, collecting data on inpatient, outpatient, accident and emergency, primary, community and social care use.

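### Psychotherapy received is monitored within the LIFE, the interview that yields both co-primary ratings, which creates a foreseeable risk of unmasking that the stated masking measures do not address

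*Protocol article*

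**What the plan says.** Four statements in the protocol article have to be read together.

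- *Outcome.* The section Co-primary mood outcome measure names the SCID-5-RV, scored by Psychiatric Status Ratings (PSR). The article describes this as a tool "which incorporates the SCID Longitudinal Follow-Up Evaluation (LIFE) [50], is used to assess the severity of depressive and manic symptoms", and gives the timing as "with measurements taken at the 27-week timepoint". It gives one depression score and one mania score.
- *Who rates, and how.* Under Assessments and outcomes: "Assessors masked to treatment group will collect outcome variables at baseline, 17-weeks, 27-weeks (after therapy cessation/TAU), and 52-weeks". The form is also given: "Assessments will be via semi-structured interviews and self-report questionnaires".
- *Treatment monitoring.* Under Control arm: TAU only: "All routine or additional treatments in both conditions will be monitored using a Treatment Documentation Sheet", with "specific treatments (anti-depressant and psychotherapy treatment) monitored within the LIFE [50] assessment tool".
- *Masking.* Randomisation and masking lists separate offices, reminders, message-taking protocols, data security, and a standard masking statement in letters to participants and clinicians. If masking breaks: "Unmasking will be recorded, and where possible an independent assessor with whom the masking has not been broken will complete follow-ups".

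The section on the intervention arm describes 26 sessions of CBT within six months, so therapy ends shortly before the primary rating. The control-arm section allows psychological treatment in usual care but describes provision for this population as poor.

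**The concern.** Participants learn their allocation by letter and therapists necessarily know it. Masking of the rater is therefore the main protection for two interviewer-judged co-primary outcomes. If the same interview asks what psychotherapy the participant has had, it solicits the one fact that best separates the arms. That is different from accidental disclosure, which the listed measures are built to prevent. A rater who forms a view of the allocation may score differently, and the ratings may then be biased, plausibly in favour of CBT. An answer given at 17 weeks could also carry over to the same assessor's rating at 27 weeks.

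**Working it through.** **1. Does the design create the route?** The co-primary scores come from the LIFE. Masked assessors collect the outcomes. Psychotherapy in both arms is monitored within the LIFE. The randomised treatment is psychotherapy. On the plain reading, the rater's own tool contains the question.

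**2. Do the stated measures close it?** Offices, message protocols and data security keep information from reaching the rater by other channels. Reminders and the letter statement ask people not to volunteer it. None covers a question that the interview itself asks. A replacement assessor comes only after the event and where possible, and would use the same tool.

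**3. How strong is the clue?** The article gives no rate of psychotherapy in usual care, so the following are assumptions. Let a be the proportion of the CBT arm reporting psychotherapy and q the proportion of the TAU arm. With equal arms, a guess based on the answer alone is right with probability 0.5a + 0.5(1 − q). For a = 0.9:

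| q | Probability of a correct guess |
|---|---|
| 0.1 | 0.45 + 0.45 = 0.90 |
| 0.3 | 0.45 + 0.35 = 0.80 |
| 0.5 | 0.45 + 0.25 = 0.70 |

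**4. The plan's own sample size.** Inputs from Sample size and power calculations: SD 1.3, baseline correlation 0.4, two-sided 2.5% level, difference 0.5, power 90%. Equal allocation is assumed because the ratio is not stated.

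- Adjusted SD = 1.3 × √(1 − 0.4²) = 1.191.
- n per arm = 2 × (2.241 + 1.282)² × 1.191² / 0.5² = 141, or 282 in total, against 286 stated.
- Power at 143 per arm is 90.4%.
- 286 / 0.85 = 336.5, so 337, or 338 for equal arms.

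The stated figures are reproduced closely. The masking point does not alter them.

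**5. What a rating shift would do.** Suppose there is no true effect and the ratings differ between arms by an average of b points. With 143 per arm, SE = 1.191 × √(2/143) = 0.141 for depression. For mania the SD is 0.5, so SE = 0.5 × √(2/143) = 0.059, or 0.054 if the 0.4 correlation is applied there too. Type I error = Φ(−2.241 + b/SE) + Φ(−2.241 − b/SE).

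| Assumed b | Depression | Mania |
|---|---|---|
| 0.05 | 3.4% | 8–9% |
| 0.10 | 6.4% | 29–35% |
| 0.20 | 21% | 87–93% |

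A shift of 0.10 would arise, for example, if half the CBT arm were rated 0.2 points lower: 0.5 × 0.2 = 0.10. That is 20% of the 0.5-point target on depression. A shift of the same absolute size weighs more on mania because its SD is smaller. Whether mania ratings would shift as far is not known.

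**The case against.** The article does not say who completes the LIFE treatment items, whether they come before or after the ratings, or whether trial CBT is left out of them. The monitoring sentence speaks of routine or additional treatments and stands in the control-arm section, so it can be read as covering non-trial treatment only. Under Measures of alliance, engagement, and adherence, therapists record CBT attendance separately. The list of masking measures is introduced as examples. The schedule figure is not reproduced, and the full protocol may settle item order and assessor instructions.

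Most of this stands, and it limits the claim. A reader might infer that the interview reveals the allocation to the assessor and that the trial result will be biased towards CBT. The documents do not support that. Usual care may include psychological treatment, referrers are told not to withhold treatment, and no rating shift is documented.

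It does not remove the point. Even if the items concern only non-trial therapy, a participant in weekly CBT who is asked about psychotherapy in a semi-structured interview has to sort trial from non-trial treatment in front of the rater. The letter statement asks participants to stay silent on a matter the interview then raises. This is an arrangement the article describes, and not merely a detail it leaves out.

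The service use questionnaire ("Service use questionnaire adapted from previous trials, collecting data on inpatient, outpatient, accident and emergency, primary, community and social care use") is a weaker route. Its description names no psychotherapy item. Antidepressants are available in both arms. Neither needs to be withdrawn on this argument.

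**Conclusion.** The point holds as a foreseeable and avoidable risk to rater masking at the primary outcome visit, which the stated measures do not address. It does not show that masking fails or that the effect estimate is biased. The size is unknown. The 6.4% figure for depression rests on an assumed 0.10-point average shift, no true effect and 143 per arm, and the mania figures rest on the same kind of assumption. The conclusion also rests on the plain reading that masked assessors administer the LIFE as a whole. If the full protocol already separates the psychotherapy items from the rater, or has them asked only after the ratings are locked and by someone who will not rate again, little remains beyond stating this in the article.

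**What to change.** For the remaining visits:

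- Take trial CBT attendance from the therapists' session records.
- Collect other psychotherapy on a form that the participant completes alone, or through staff who already know the allocation.
- Have the assessor record and lock both PSRs before seeing any treatment information.
- Keep the antidepressant and service-use items, but ask them after the PSRs are locked. The antidepressant data are needed for the planned analyses of intervention receipt.
- Report recorded unmasking by arm. Treat any analysis limited to ratings made while masked as exploratory: unmasking happens after randomisation and probably more often in the CBT arm, so excluding those ratings could itself introduce selection bias.

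The cost is a reordered case report form and a working instruction, plus some staff time if allocation-aware staff collect the items. Self-reported psychotherapy data may be slightly less complete, and collection will differ between earlier and later visits. Trial Status gives July 2025 as the end of recruitment, so the change can protect only visits still outstanding. Reporting unmasking by arm remains open for all participants.
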